### WP-III

This embedded qualitative study, which assesses the experiences of the parents and clinicians about their involvement in the REPORT-BPD study, will provide an important insight into the different aspects of the study, such as the effectiveness of the recruitment process and the acceptability of the procedures [26]. In addition, this qualitative work, as part of the REPORT-BPD study, will be crucial in evaluating the perception of the study participants (parents and clinicians) regarding the study processes and investigations used (e.g. the echo scans), which will be important to inform the design of a larger study [27].

#### Objectives

To explore the experiences of parents in participating in the REPORT-BPD feasibility studyTo explore the experiences of healthcare professionals in participating in the feasibility study as part of the neonatal research team

#### Study design and settings

This is an additional qualitative research project of the REPORT-BPD study that explores the parents’ and healthcare professionals’ experiences of the REPORT-BPD feasibility study using semi-structured interviews.

This additional qualitative work, as part of the REPORT-BPD study, will be conducted at the regional tertiary NICU, UHP, Plymouth.

#### Recruitment

Purposive stratified sampling of the participants will be undertaken. In qualitative research methods, a sample size of between 5 and 25 participants is generally accepted to reach data saturation depending on the study phenomenon [28]. Therefore, the research team will aim to recruit 10–15 parents and 10–15 healthcare professionals depending on the data saturation. The clinicians’ sample will be made consistent with that of the doctors and nurses involved in the REPORT-BPD study as part of the neonatal research team at any stage from recruitment, enrolment or data collection.

##### Inclusion criteria

Parents’ inclusion criteriaTheir infants are recruited for the REPORT-BPD feasibility studyThey speak English

Healthcare professionals’ inclusion criteriaA staff member involved in the REPORT-BPD feasibility study procedures, such as screening, recruitment and data collection, as part of the neonatal research team

##### Exclusion criteria

Parents’ exclusion criteriaNon-English speakingParents whose child has diedParents who have withdrawn from the study

Healthcare professionals’ exclusion criteriaTemporary staff members, such as locum or bank staff

The eligibility assessment of the recruited preterm infants’ parents will be conducted 2–3 days prior to the last echo scan on the 9th day of postnatal life.

The chief investigator (CI) will identify healthcare professionals who participated in the REPORT-BPD feasibility study by reviewing the delegation log register.

Taking the consent of eligible participants to participate in this qualitative research as part of the REPORT-BPD study will not start until 50% of the WP-I and II recruitment target is achieved.

##### Parents’ consent

Eligible parents of preterm infants recruited for the REPORT-BPD feasibility study WP-I and WP-II will be invited by the CI to participate in this qualitative research as part of the REPORT-BPD study. A PIS for this qualitative research project will be provided to the parents during an initial brief face-to-face conversation with the CI. If the parents are interested in participating, the CI will meet them to address their queries and ask them to sign the ICF. Interviews will be conducted within 7 days of obtaining their consent.

##### Clinicians’ consent

Eligible clinicians involved in the initial phases of the REPORT-BPD feasibility study will be invited to participate in this qualitative research by the CI and given the study PIS. The staff members who express their interest in participating in this qualitative research will meet the CI so that their queries can be answered. They will be asked to sign the ICF if they agree to participate. The interviews will be conducted within one month of obtaining their consent.

#### Data collection and analysis

Semi-structured interviews will be conducted to ensure freedom for participants to express their views and to provide an opportunity for the interviewer to ask in-depth questions [29]. The semi-structured interview style will be used due to its exploratory nature with more flexibility compared to a structured interview. It is also more standardised than an unstructured interview [30]. The Cl aims to recruit between 10 and 15 parents and 10 and 15 clinicians depending on the saturation. In the 10th interview, data saturation will be assessed. Data saturation is defined as acquiring enough information to reproduce the study, when the ability to obtain additional information has been accomplished and when further coding is no longer possible [31].

##### Parents’ interviews

Semi-structured interviews will be conducted in a quiet and private place in the NICU at a time convenient for parents.

Both parents will be invited. When both parents are recruited, they will be interviewed separately to obtain individual perspectives and both parents might be unwilling to leave their infant’s bed space simultaneously. The study team will aim to have a balanced recruitment of both parents in the study, since fathers historically are less likely to consent for an interview [32].

##### Clinicians’ interviews

Similar to the parents, the interviews will be semi-structured. The CI will conduct one-to-one interviews in a quiet and private place in the NICU at a time convenient for the recruited clinicians.

Since many team members will be available to look after the study infants during the study procedure, it is important to gather the information from various clinicians, such as nurses, advanced nurse practitioners and doctors at different levels of seniority. The staff members will be identified through the delegation log.

The parents’ and health professionals’ interviews are expected to last approximately 30–45 min using the semi-structured interview guidelines. The interviews will be audio-recorded and transcribed by the CI. Field notes will be completed immediately after the interviews, along with a reflective diary of how the interviewer felt during the interview, which will be used during the data analysis.

Interview guides were developed using the concepts identified in a literature review by O’Cathain et al. [18].

##### Member checking

‘Member checking’ will be used in this phase of the research project to enhance credibility of the qualitative data of WP-III. This method is used to augment the trustworthiness of the extracted data [33].

The focus will be on member checking of the transcripts verbatim only; thus, each participant interview will provide the opportunity to check the transcripts, make amendments, add explanations and see if it is a true reflection of their experiences. Member checking will not be performed on the analysis of the data report for the following reasons. First, the data analysis report will not be available until several months after the data collection (i.e. when the preterm infants are discharged); this might increase the loss to follow-up risk [33]. Second, the process is quite time-consuming for the participants [33]. This might be challenging for the parents who are looking to spend quality time with their children after a lengthy stay at the neonatal unit. Third, sending data analysis reports to the participants might remind them of previous difficult times, which raises ethical concerns as researchers should aim to diminish distress to participants [33].

The member checking process for the interview verbatim transcripts will be performed by giving the participants hard copies of the transcripts to review within 1–2 weeks after their semi-structured interview.

These transcripts will be imported into NVivo to enable the organisation and analysis of textual data. A thematic analysis will be deployed and comprise six steps [25], as detailed in the WP-II data collection and analysis section.

The analysis of interviews of WPIII will enable the study team to unveil any inadequacies of the study processes, such as screening and recruitment, identified by the parents and healthcare professionals so adjustments can be implemented to augment the recruitment and retention rates of the future definitive study.

Study recruitment will be conducted over 18 months. WP-I and WP-II recruitment will be conducted during this period, while WP-III recruitment will be conducted during the second half. The results are expected to be submitted for publication by mid-2024. The outcome measures are detailed in Table 3.

**Table 3 Tab3:** Outcome measures for all the three WPs

Work package	Outcome measures
**Work package—I**	• Establishing sensitive and feasible echo parameters for detecting right ventricle dysfunction associated with early BPD pulmonary vascular changes • Suitability of eligibility criteria and sample characteristics • Fidelity to the study procedures such as recruitment, data collection including echo scan performance at the set time points • Recruitment, accrual, and retention rates
**Work package—II**	• To gain an understanding of how strong the correlation between the parents’ views of their infant’s health development during the first 10 days of postnatal life and the findings of echo scans at the same period
**Work package—III**	• To gain an understanding of parents and healthcare professionals in participating in the study and identify barriers and enabling factors to inform the methods a full trial

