### WP-II

This WP will examine the parental notes written in their preterm infants’ NICU diary. The parental diary in the intensive care setting is used to help parents cope with the situation by writing down their feelings [23, 24]. There is a paucity of research project regarding the use of parental perceptions recorded in the NICU diary about their children’s health. Therefore, the diary recordings of the participating preterm infants’ parents about the respiratory function changes observed by the parents in the first 10 DABs will help in understanding the significance of parental perception of the progression of their infants regarding the respiratory function. Mining and examining these data will highlight the strength of the correlation between the parental observations of their children’s health in the first 10 DABs in recognising early BPD symptoms.

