#### Objectives

To understand parental perceptions regarding their preterm infants’ health progression in the first 10 days of postnatal life and its correlation with the echo scans findings.

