#### Study design and settings

This is an embedded qualitative study that explores the parental perception of their infants’ health written in a diary.

This study will be conducted in the regional tertiary NICU, UHP, Plymouth.

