#### Data collection and analysis

Once consent is obtained from the parents on the second DAB of their infants, the research team will give the parents a NICU diary along with a study leaflet about ‘how to write a NICU diary’. The diary comprises a small notebook consists of 50 blank pages. A NICU diary writing guide will be given to parents advising what they might write in NICU diary such as reflections, feelings, comments about their child health and progress. There are no limitations on the frequency of notetaking by parents, i.e. they can choose to write as little or as much as possible. On the 10th DAB, the research team will obtain a copy of the parental notes documented in their preterm infants’ NICU diary from the 2nd to 10th DAB, as the original copy is for their keepsake. Therefore, only the records of the NICU diary within the first 10 DABs will be collected. The parental notes written in the NICU diary will be transcribed for analysis.

The transcripts will be imported into the qualitative analysis software programme NVivo to enable the organisation and analysis of textual data. A thematic analysis will be deployed and comprise the following six steps [25]. The first step will involve familiarisation with the text, where two researchers ([name] (WM) and [name] (JL)) will independently read the transcripts. In the next step, these researchers will independently code the text by allocating text fragments to codes. The codes might be revised during the process of reading the transcripts. In step three, the two researchers will discuss the results of individual codes (sub-themes) and refocus their analysis on identifying potential themes. Step four will involve two levels: level 1 will involve scrutinising the identified themes to generate an accurate thematic map, and in level 2, the researchers will examine whether the generated thematic map accurately reflects the codes extracted from the datasets. The fifth step will involve defining and naming the themes by further refining them. Finally, the sixth step will involve creating the final report, which will be focused on writing a concise, coherent, logical, non-repetitive and interesting account of the data story [25].

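### Work package II's only listed outcome is the strength of a correlation, but no analysis step described would produce one

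*Protocol article*

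**What the plan says.** **The promise.** Three places in the protocol article state it.

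- Table 3, WP-II row, lists a single outcome measure, which opens "To gain an understanding of how strong the correlation between the". The entry then names the two sides of the correlation: parents' views of their infant's health over the first 10 days, and the echo findings over the same period.
- WP-II, Objectives, pairs parental perceptions of the infant's progress with "its correlation with the echo scans findings".
- WP-II, introductory paragraph: "Mining and examining these data will highlight the strength of the correlation between the parental observations of their children’s health in the first 10 DABs". Here the other side is the recognition of early BPD symptoms, not echo findings.

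**The method.** WP-II, Study design and settings, describes the work package this way: "This is an embedded qualitative study that explores the parental perception of their infants’ health written in a diary". Under WP-II, Data collection and analysis, the instrument is a blank notebook. A guide suggests what parents might write, and on frequency "they can choose to write as little or as much as possible". The copy taken covers days 2 to 10. The analysis is introduced with "A thematic analysis will be deployed and comprise the following six steps", and all six steps are then set out. Two researchers read and code the transcripts independently in the first two steps.

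**The concern.** Asking how strong a correlation is asks for a magnitude. A magnitude needs a value per infant on each side and a rule for relating them. The echo side has measurements, but the diary side has only text, and the described analysis turns text into themes and a report.

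If the plan is followed as written, either the outcome in Table 3 goes unreported or an impression of agreement is reported in the language of correlation. If a score is devised later to fill the gap, it could be built after the echo results and BPD status are known, when the choice of score can be swayed by what it is meant to correlate with. The comparator is also unsettled, because two places name echo findings and one names early BPD symptoms.

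**Working it through.** The article gives no correlation, power or sample-size figure for WP-II, so there is nothing to reproduce. The check sets what a correlation needs beside what the article provides.

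| Needed to report a strength of correlation | What the article describes |
|---|---|
| A diary value for each infant | None. Blank pages, optional content and frequency, no rating or item (WP-II, Data collection and analysis) |
| A step turning codes into that value | None. The six steps are familiarisation, coding, finding themes, checking a thematic map, naming themes, writing the report |
| One comparator | Echo findings (Objectives; Table 3) or early BPD symptoms (WP-II introduction) |
| A chosen echo parameter and scan day | None for WP-II. WP-I collects many parameters on days 5 and 9 |
| A step linking diary to comparator | None |
| A measure of association | None. The t-tests, Mann–Whitney U tests and chi-squared tests under WP-I, Data collection and analysis, compare WP-I measurements between the BPD groups and do not use the diaries |

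The number of correlation estimates that the described steps would yield is therefore zero.

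**Illustration of precision if a score were added.** Two assumptions here are not in the article: one score per infant, and an observed correlation of r = 0.3. The number of diaries, n = 40, is the WP-II target (WP-II, Recruitment). It is a ceiling, since non-English-speaking parents are excluded and the article allows for fewer.

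The approximate 95% interval is tanh(atanh(r) ± 1.96/√(n − 3)).

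- atanh(0.3) = 0.3095
- 1.96/√37 = 0.3222
- Lower limit: tanh(0.3095 − 0.3222) = tanh(−0.0127) = −0.01
- Upper limit: tanh(0.3095 + 0.3222) = tanh(0.6317) = 0.56

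Other values from the same formula show the range:

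| n | r = 0 | r = 0.3 | r = 0.5 |
|---|---|---|---|
| 40 | −0.31 to 0.31 | −0.01 to 0.56 | 0.22 to 0.70 |
| 20 | −0.44 to 0.44 | −0.16 to 0.66 | 0.07 to 0.77 |

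This is the interval for a Pearson correlation. A Spearman interval is usually somewhat wider. The finding does not rest on these figures. They show only that a scored version would give an imprecise answer.

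**The case against.** The best defence is that correlation is used loosely. WP-II is labelled qualitative, its objective opens with understanding perceptions, and the Table 3 entry speaks of gaining an understanding. On that reading, concordance between themes and echo findings is all that is meant. This is plausible, but Table 3 asks how strong the relation is and the introduction speaks of its strength, and both are terms of magnitude. If concordance is the intention, the repair is a change of wording.

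A second defence is that a journal article condenses a fuller protocol, which might hold the linking step. That would carry weight if the method were only sketched. Here the whole six-step sequence is set out, and it does not fit the outcome beside it. That is a mismatch between two stated things, not an omitted detail.

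Three stronger readings are tempting, and the document does not support them.

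- **That the question is unanswerable in principle.** It is not. Independently coded transcripts can be turned into per-infant variables, such as a theme being present or absent, and related to echo data. The article simply does not say that this will be done.
- **That the diaries are contaminated by known scan results.** Copies do include entries written after the day-5 and day-9 scans. The scans must be clinically indicated (Table 2), and the research team is also part of the clinical team, so parents could learn results. The article does not say that they do, or that the coders see echo data. This is a reason for a precaution, not an established bias.
- **That WP-II as a whole fails.** Thematic analysis is suited to the first half of the objective, understanding parental perceptions.

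**Conclusion.** The point holds for the plan as described. The only outcome measure listed for WP-II is the strength of a correlation, and no described step produces a diary measure or relates it to echo or BPD data. The consequence is confined to that outcome: no estimate would be delivered. The perceptions aim is served, and the primary outcome, secondary outcomes and progression criteria listed for the study do not use the diaries.

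The conclusion rests on reading the six steps as the complete WP-II analysis, which is how the article presents them. It does not depend on any assumed correlation or number of diaries. It should be corrected before the diaries are analysed, because a score defined after the echo and BPD results are known would be hard to defend.

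**What to change.** Choose one of two options.

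**(a) Add a quantifying step.**

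1. Ask parents to date their entries. The article states no such requirement.
2. Before seeing any echo or BPD data, have the two existing coders independently rate each diary on a pre-specified ordinal scale of reported respiratory concern. Report their agreement, and state in advance how the two ratings are combined.
3. Report Spearman's correlation with its 95% confidence interval against one RV parameter and one scan day, both fixed in advance. The parameter that WP-I finds most sensitive should not be used by default, because it is selected on the same infants.
4. Report the same score against BPD group, to cover the aim in the WP-II introduction.
5. Label all of this exploratory.
6. As a precaution, separate entries written before and after each scan. Collection starts on day 2, so only days 2, 3 and 4 precede the day of the first scan, and that window may be sparse.

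The cost is modest coding time for up to 40 diaries, missing scores where parents wrote little, and an imprecise estimate.

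**(b) Reword.** Remove the language of correlation and strength from the WP-II introduction, the WP-II objective and Table 3. State the outcome as a qualitative exploration of whether diary themes agree with echo findings, with no claim of strength. This costs wording only, and gives up any quantitative statement about the diaries.

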## Discussion

The current scientific literature shows that early BPD starts in the first WAB of the affected preterm infants, with the respiratory function decline manifesting at the 7th day of postnatal life [17]. In addition, animal research findings support the vascular theory, indicating that the vascular changes in early BPD start before the pulmonary parenchymal ones [4]. These findings form the foundation for structuring the proposed study. The research team will perform two echo scans two days before and after the 7th DAB. This will allow a closer examination of RV functional changes in preterm infants with early BPD compared to healthy ones.

The strengths of this study can be summarised as follows. First, it uses two echo scans around the timepoint of change in the pulmonary function. Second, it uses only non-invasive intervention (echo scans). Our tertiary NICU is well-positioned to conduct the study since our experienced neonatal team regularly performs haemodynamic assessments with functional neonatal echo scans. Third, a combination of advanced technologies will be used to assess the RV function (e.g. TDI and speckle tracking). The proposed study will not only highlight the most sensitive echo parameters through the study analysis but also help in identifying if one echo scan, either day 5 or 7 of postnatal life, is adequate to diagnose the early BPD-associated RV dysfunction.

The functional echocardiographic examinations of ductus arteriosus and pulmonary arterial pressure will allow the study team to investigate its effect on the echo parameters related to the RV function in preterm infants with BPD and controls.

The main limitation of the study is that it is an observational study since a randomised controlled trial is not an appropriate design to answer our research question.

To the best of our knowledge, this is the first study performing two echo assessments at 5th and 9th DABs using a combination of the most recent cardiac technologies to analyse the acquired neonatal echo scans. The study findings will allow the formulation of an early BPD predictive model. The future plan is to test this model in a large multi-centre trial.

## Data Availability

Not applicable.

